## Abstract

**Background:**

Depression has become one of the leading contributors to the global disease burden. Evidence-based treatments for depression are available, but access to them is still limited in some instances. As technology has become more integrated into mental health care, computerized cognitive behavioral therapy (CBT) protocols have become available and have been recently transposed to mobile environments (e.g., smartphones) in the form of “apps.” Preliminary research on some depression apps has shown promising results in reducing subthreshold or mild to moderate depressive symptoms. However, this small number of studies reports a low statistical power and they have not yet been replicated. Moreover, none of them included an active placebo comparison group. This is problematic, as a “digital placebo effect” may explain some of the positive effects documented until now. The aim of this study is to test a newly developed mobile app firmly grounded in the CBT theory of depression to determine whether this app is clinically useful in decreasing moderate depressive symptoms when compared with an active placebo. Additionally, we are interested in the app’s effect on emotional wellbeing and depressogenic cognitions.

**Methods/design:**

Romanian-speaking adults (18 years and older) with access to a computer and the Internet and owning a smartphone are included in the study. A randomized, three-arm clinical trial is being conducted (i.e., active intervention, placebo intervention and delayed intervention). Two hundred and twenty participants with moderate depressive symptoms (i.e., obtaining scores >9 and ≤16 on the Patient Health Questionnaire, PHQ-9) will be randomized to the three conditions. Participants undergoing therapy, presenting serious mental health problems, or legal or health issues that would prevent them from using the app, as well as participants reporting suicidal ideation are excluded. Participants randomized to the active and placebo interventions will use the smartphone app for 6 weeks. A short therapist check-in via phone will take place every week. Participants in the delayed-intervention condition will be given access to the app after 6 weeks from randomization. The primary outcome is the level of depressive symptomatology. The intervention delivered through the app to the active condition includes psychoeducational materials and exercises based on CBT for depression, while the placebo intervention uses a sham version of the app (i.e., similar structure of courses and exercises).

**Discussion:**

To our knowledge, this study protocol is the first to test the efficacy of a smartphone app for depressive symptomatology in the form of a randomized controlled trial (RCT) that includes an active placebo condition. As such, this can substantially add to the body of evidence supporting the use of apps designed to decrease depression.

**Trial registration:**

ClinicalTrials.gov, identifier: NCT03060200. Registered on 1 February 2017. The first participant was enrolled on 17 February 2017.

**Electronic supplementary material:**

The online version of this article (doi:10.1186/s13063-017-1960-1) contains supplementary material, which is available to authorized users.

## Background

Depression is a highly prevalent and burdensome condition worldwide. According to the World Health Organization, by 2030 depression will be the main contributor to the global disease burden (GDB) [1].

While effective, evidence-based treatments for depression do exist, they are sometimes not accessed appropriately due to a variety of reasons. In fact, fewer than half of those in need of treatment (and in many countries, fewer than 10%) receive adequate care [2]. Barriers to treatment access include stigma, logistical costs, or the limited availability of adequately trained therapists [3, 4]. In this context, increasing treatment accessibility for people suffering from depression is critical.

As technology has become more integrated into mental health care [5, 6] and Internet access has increased [7], computerized treatment protocols have been proposed as potential solutions to overcome the issue of treatment accessibility [8–11]. Cognitive behavioral therapy (CBT), one of the best empirically supported psychological treatments for depression [12], has been adapted for online formats, and research has shown that computerized CBT protocols for depression could yield results comparable to face-to-face CBT in both adult and youth samples [13, 14]. Furthermore, computerized CBT programs for depression show a higher moderate effect size compared to control conditions, with even better results in the case of assisted programs [15]. Yet, many studies testing computerized CBT for depression are of low quality, few included an active placebo group, and even fewer have investigated the mechanisms of change [16]. Moreover, the benefits of treatment have been reported to be rather short lived, the impact on functioning was found to be minimal, and high attrition rates seriously limited the potential clinical benefits [17]. However, in the rush to develop highly accessible, attractive and flexible technological solutions for mental health problems, the problems associated with computerized CBT for depression have been largely ignored.

### Framework and rationale of the present study

In the recent years, some computerized CBT protocols have transitioned to mobile environments (e.g., smartphones) in the form of “apps.” These apps have been designed to allow an even more flexible and personalized treatment for depression. However, since very few of them have ever been tested in randomized clinical trials [18] it is largely unclear if they are beneficial, or, perhaps more importantly, if they might have unintended side effects. Some of these apps claim to provide elements congruent to the best practice guidelines in the field (e.g., being CBT-inspired), but they vary widely in scope, content, and complexity. To our knowledge, none has provided comprehensive evidence-based support for their efficacy.

Several preliminary studies on some depression apps have shown promising results in reducing subthreshold or mild to moderate depressive symptoms [19–24]. Still, such studies are small (pilot studies), too few, and not replicated [18]. Moreover, none of them included an active placebo comparison group. This is problematic, as a “digital placebo effect” may explain – at least partially – some of the positive effects documented by the few existing studies [18]. Such placebo effects could be the result of a variety of factors such as cognitive distraction, behavioral activation (BA), positive expectations (demand effects), the perception of the smartphone as being an extension of self (which could result in feeling better just because the person receives messages and advice through a familiar, personal device; [18] or a combination of these.

In short, the evidence supporting the use of apps designed to decrease depression is mounting, but consistent, additional, experimentally sound work is needed before we can draw clear conclusions.

### Objectives

To discern between a genuine clinical effect and a placebo effect, we need to compare outcomes from participants using an actual app with those from participants using a sham version of it. The present study has been designed specifically to achieve this desiderate. We aim to test a newly developed mobile app firmly grounded in the CBT theory of depression to determine whether this app is clinically useful in decreasing moderate depressive symptoms when compared with an active placebo. Additionally, we are interested in the app’s potential to contribute to the reduction of general negative affect, increasing positive affect, and boosting satisfaction with life. Last, but not least, we aim to verify whether the usage of the tested app can modify depressogenic cognitions.

## Methods/design

### Trial design

This study is a randomized, placebo-controlled trial examining the effects of an mHealth CBT intervention in reducing depressive symptomatology for people with moderate symptoms. Participants are randomly assigned to one of the three arms of the trial: (1) mHealth CBT intervention, (2) placebo intervention (PI), and (3) delayed intervention (wait-list; WL). Major assessments are at baseline, mid-intervention, post intervention, and 3-month follow-up. The participants randomized to the PI and WL trial arms are offered access to the mHealth app upon the completion of the study.

The Consolidated Standards of Reporting Trials (CONSORT) guidelines [25] and the Standard Protocol Items: Recommendations for Interventional Trials (SPIRIT) Statement 2013 [26] are followed (see also Additional file 1: SPIRIT 2013 Checklist: recommended items to address in a clinical trial protocol and related documents).

Participants are blinded to the nature of the placebo intervention, but they are informed that they have a 1 in 3 chance of being assigned to the PI group.

### Generic description of the tested application

DCombat is an innovative smartphone app that uses the basic principles of CBT in treating depressive symptoms. It is available for download for iOS and Android and has the following features:Profile and overview section: following the login, the first screen of the application (“profile” or homepage) offers the user the possibility of choosing and personalizing an avatar. On subsequent occasions, at every login, this first screen summarizes information about the user’s activity and therapeutic progress in a simple and attractive format: the user can check their current “energy level” reached from using the app, their progress through its contents. The app incorporates an attractive design in both the visual presentation and flow of activities [27, 28]. Borrowing from gamification strategies [29], the app integrates two graphical representations similar to role-play games: “Energy” and “Level.” Energy represents a percentage value that decreases over time if the app is not used. The objective is to keep the energy level as close to 100% as possible. Reading articles, completing CBT-inspired exercises and filling out questionnaires are all rewarded with an energy boost. Level represents the user’s progress through the educational articles – reading each article increases the level by 1. The goal is to reach the maximum level (i.e., level 12). The overview provided on the first screen also includes a chart representing the user’s progress in improving their mood over time, measured via a scale in the Evaluation section. The overview screen also provides tasks (similar to homework assigned used in face-to-face therapy) in the form of “missions” that are to be completed by the user. Over the course of the program different missions encourage the users to read articles, fill out questionnaires, plan daily activities, and practice rational thinking by doing the existing exercises. When completing missions users are awarded with “achievements” that provide positive feedback. Achievements are always presented on the profile screen to further incentivize and reward consistent app usage. (see Fig. 1 below, for an example of the profile and overview section)

**Fig. 1 Fig1:**
[figure not shown]
App screenshot with the “profile” and overview sectionPsychoeducation section: this section contains articles and self-help materials covering topics such as the causes of depression, the impact of dysfunctional thinking patterns and unproductive behaviors, healthy and unhealthy negative emotions, as well as a series of educational videos about relaxation techniquesExercises: the app contains a series of guided cognitive restructuring and behavioral activation (BA) exercises, following the ABCDE model of emotional disturbance [30, 31], and the Brief Behavioral Activation Treatment for Depression described by Lejuez, Hopko, and Hopko [32], respectively. The cognitive restructuring exercises are based on a model where each emotion is assigned to several activating events and the specific underlying rational/irrational beliefs – so that the user is automatically guided through rational thinking patterns without the need for therapist feedback. The BA exercises allow the user to insert content in specific exercise tabs designed around goals, and pleasant activities to be used in the pursuit of these goals (see Fig. 2 for an overview of the “Exercises” section). Completing each activity and exercise is rewarded graphically through a notification and an increase of the Energy percentage (see Fig. 3 below, for an example of the Exercises section – cognitive restructuring exercise)

**Fig. 2 Fig2:**
[figure not shown]
App screenshot of the “Exercises” section

**Fig. 3 Fig3:**
[figure not shown]
App screenshot of a cognitive restructuring exercise sequenceEvaluation section: within the app, the user can fill out questionnaires related to the study being conducted which include a mood inventory. The mood inventory updates the progress graph on the profile section, described earlier. Whenever a new evaluation is due, the user is notified and rewarded with more Energy after completing it.“Messages” section: each week the users are encouraged, via automated messages, to read articles and use the exercises available. They are also reminded to complete that week’s assessment. Moreover, this section allows them to send messages to the research team regarding technical difficulties or other obstacles encountered in using the application’s interface. The user can also use this feature for clinical support or guidance.

### Study setting

The study population consists of Romanian adults with moderate depressive symptomatology. The study is being implemented through the Babeș-Bolyai University, Cluj-Napoca, Romania.

#### Eligibility criteria

##### Inclusion criteria

Healthy Romanian-speaking adults (18 years or older), with access to a computer, a smartphone (Android or iOS), and the Internet are included in the study. The Structured Clinical Interview for *Diagnostic and Statistical Manual of Mental Disorders, Fourth Edition, Text Revision* (DSM-IV) (SCID) [33], specifically, the Overview Module will be used to determine the general clinical status of the participants. A clinical psychologist will conduct a short interview aimed to screen for exclusion criteria (see below). Information on drug use and physical and psychological treatment status will be collected. In addition, to be included in the study, participants should report a Patient Health Questionnaire-9 (PHQ-9) score above 9, but no greater than 16.

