#### Measures of primary, secondary, and other outcomes

The following measures have been adapted into Romanian and successfully used in two previous trials testing another version of the app, and they have shown adequate psychometric properties [36].

The level of depressive symptomatology is assessed with the Center for Epidemiologic Studies Depression Scale–Revised (CESD-R) [37, 38]. The CESD-R is a 20-item self-report instrument, which measures symptoms of depression in nine different groups: sadness (dysphoria), loss of interest (anhedonia), appetite, sleep, thinking/concentration, guilt (worthlessness), tiredness (fatigue), movement (agitation), and suicidal ideation. Participants rate each item on a 5-point Likert scale, from 0 (not at all or less than 1 day) to 4 (nearly every day for 2 weeks) to indicate how they felt or behaved during the last week or so. The total CESD-R score is calculated as a sum of responses to all 20 questions. The CESD-R exhibited good psychometric properties, including high internal consistency, strong factor loadings, and theoretically consistent convergent and divergent validity with anxiety, schizotypy, and positive and negative affect [39].

*The Positive and Negative Affect Scale* (PANAS) [40] is a 20-item self-report questionnaire designed to assess mood. It consists of 10 items that address positive affect (PA) and 10 items that address negative affect (NA). Participants rate each item on a 5-point Likert scale, from 1 (very slightly/not at all) to 5 (extremely) to indicate how they felt during the indicated time frame. The PANAS can be used to assess mood on various time scales by altering the instructions. For the purposes of this study we have used a 2-week time frame. The validity and internal consistency of the PANAS are good, with test-retest reliability being the highest for the “general” temporal instruction. The PANAS has been used previously on the Romanian population and was found to have adequate psychometric properties [41, 42].

*Satisfaction with Life* (SWL) [43] is a five-item scale designed to measure global cognitive judgments of one’s life satisfaction. Participants rate each of the five items using a 7-point scale that ranges from 7 (strongly agree) to 1 (strongly disagree). The SWL has been shown to be a valid and reliable measure of life satisfaction which can be used with a wide range of age groups [44, 45].

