#### Participant timeline

Potential participants will be assessed for eligibility through an initial assessment of depressive symptoms. The initial assessment phase consists of administration of the PHQ-9 and a short phone screening interview. Applicants who do not meet the inclusion criteria are informed via e-mail. They are given a summary score and interpretation for their PHQ-9 score and they are encouraged to discuss their problems with a professional, if necessary. Information on how to reach one – a clinical psychologist or a psychotherapist – is also provided.

After the initial assessment, the participants meeting the inclusion criteria will be randomly assigned to one of the three conditions: (1) active intervention condition – mHealth CBT (group 1), (2) the PI (group 2), or (3) the delayed-intervention condition (WL) (group 3) (see flow diagram in Fig. 4). Subsequent assessments consist of all the instruments presented in the “Outcome measures” section. Figure 5 shows the schedule of enrollment, interventions, and assessments which accords with the SPIRIT figure.

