### Assignment to study group

The participants are randomly assigned to one of the three trial arms, using the software Randomizer.org. Randomization is performed by a research assistant using a simple (unrestricted) randomization sequence that assigns three unique numbers per participant; the number assigned is either 1, 2, or 3 according to the number of the experimental condition. To conceal the allocation mechanism, the same research assistant will monitor the assessments and allow access to the application for the participants in the wait-list control group after 6 weeks. The principal investigator and the statisticians running the data analysis will remain blinded to the study condition until the completion of the study.

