### Data collection, management, and analyses

#### Data collection methods

The initial assessment data are collected via the project website. Afterwards, a research assistant conducts telephone-screening interviews with potential participants to determine eligibility, and provides clinical screening reports. All subsequent assessment data are collected within the application, in the Evaluation section, and transferred to our servers using an encrypted, secure (https) industry-standard transfer protocol.

As far as participant retention and follow-up completion are concerned, the therapist check-in component of both the active and placebo interventions will play an important role. Besides being reminded of the specific assessment that needs to be completed after each intervention module, through the Messages section, the participants will also be encouraged by their assigned therapist to complete the assessments. Also, the therapist informs them that the weekly completion of the mood questionnaires allows the app to create a personalized profile of their mood, along with individualized visual feedback on their emotional state. Moreover, they are rewarded with more Energy after completing every assessment. Finally, for the follow-up assessments, the participants will receive new messages reminding them that free use of the app was possible because of a research grant, and thus data collection is essential. Additionally, participants are informed that they can attend an online psychological assessment with a clinical psychologist, based on the completion of follow-up questionnaires, if they wish to do so.

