#### Statistical methods

Post-treatment analyses involve an intent-to-treat (ITT) design with the first available data after the baseline carried forward.

Improvement in the primary outcomes measures scores within and between the groups will be examined using mixed-effects linear regression analyses with a random intercept and slope over time (four assessments: baseline, mid-intervention, post intervention, and follow-up) and fixed effects for intervention assignment. The main analysis will compare groups (active intervention, PI, and WL) in terms of the level of depressive symptoms. When the analysis of secondary/other outcomes is performed, the error probability will be adjusted according to the number of group comparisons performed.

App usage data and user activity will be examined by comparing, for example, the participants’ self-reported activity with their actual app usage as recorded by our software. This will inform us about any obstacles to user adherence to the protocol, as well as specific usage patterns.

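### The stated primary model makes no use of the screening PHQ-9, the one symptom score clearly taken before allocation; adding it is a free, mostly small gain

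*Protocol article*

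**What the plan says.** - **Entry score.** Inclusion criteria: "to be included in the study, participants should report a Patient Health Questionnaire-9 (PHQ-9) score above 9, but no greater than 16". On whole-number scores this means 10 to 16.
- **Timing.** Participant timeline: "The initial assessment phase consists of administration of the PHQ-9 and a short phone screening interview". The same section continues: "After the initial assessment, the participants meeting the inclusion criteria will be randomly assigned to one of the three conditions". The PHQ-9 thus precedes allocation and is complete for everyone randomised.
- **Role.** The article lists the PHQ-9 only under Screening measures. The primary outcome is measured with a different scale, the CESD-R.
- **Allocation.** Assignment to study group describes randomisation "using a simple (unrestricted) randomization sequence". No stratification by severity is mentioned.
- **Primary model.** Statistical methods describes a mixed-effects linear regression with a random intercept and slope over four assessments, the first of them baseline, and "fixed effects for intervention assignment". It names no covariate and no group-by-time term.
- **Collection of the other scores.** Data collection methods, after describing the initial website assessment and telephone screening: "All subsequent assessment data are collected within the application, in the Evaluation section".

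**The concern.** The PHQ-9 measures the same construct as the primary outcome, is already held for everyone, and cannot be affected by arm. Leaving a prognostic covariate out of the model keeps between-person variance in the app-versus-placebo estimate that could be removed at no cost. Because allocation is unrestricted, the design does not balance severity either.

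The PHQ-9 matters in particular because it is the only depression score that the article clearly places before allocation. Participant timeline and Data collection methods together suggest that baseline CESD-R is collected in the app after assignment. If so, it could be missing, or influenced by knowledge of the arm, in a way that the PHQ-9 cannot.

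At stake is some precision for the comparison that the Objectives section puts first, app against active placebo.

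**Working it through.** **1. The plan's own figure.** Sample size gives N = 165 for alpha 0.05, power 0.80, f = 0.2, repeated-measures ANOVA, between factors. The number of measurements m and their correlation rho are not stated. With three arms and assumed m = 3, rho = 0.5:

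lambda = N f² m / (1 + (m − 1) rho) = 165 × 0.04 × 3 / 2 = 9.9, with 2 and 162 degrees of freedom.

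The noncentral F distribution gives power 0.804, and 165 is the smallest multiple of 3 that reaches 0.80. The figure reproduces.

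**2. Assumptions for the gain.** The article gives no PHQ-9/CESD-R correlation. I assume:
- CESD-R at times 1, 2, 3 with unit variances and correlations 0.6 (times 1-2), 0.5 (times 1-3) and 0.6 (times 2-3), matrix V;
- PHQ-9 correlations with CESD-R at times 1, 2, 3, restricted to scores 10-16, of c = (0.25, 0.20, 0.20), (0.35, 0.30, 0.30) or (0.40, 0.37, 0.37).

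Time 4 is left out because the wait-list arm has no such assessment.

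**3. Literal reading: group main effect over visits.** Per-person variance of the level is 1/(1'V⁻¹1) without the PHQ-9, and the same expression with V − cc' after adjusting for it. Without the PHQ-9 it is 0.709.

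| c | Variance with PHQ-9 | Reduction | Equivalent extra participants, 220/(1 − reduction) − 220 |
|---|---|---|---|
| low | 0.661 | 6.7% | 16 |
| middle | 0.607 | 14.3% | 37 |
| high | 0.564 | 20.5% | 57 |

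**4. Group-by-time reading: week 6 minus baseline.** The variance of the change is 2 − 2 × 0.5 = 1. A PHQ-9 main effect cancels from the difference and removes nothing. A PHQ-9-by-visit term removes (c3 − c1)² / 1 = 0.05², 0.05², 0.03², which is 0.25%, 0.25% and 0.09%.

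**5. Baseline CESD-R as a covariate.** The variance at week 6 given baseline is 1 − 0.5² = 0.750. Adding the PHQ-9 gives 0.744, 0.732 and 0.716, reductions of 0.8%, 2.4% and 4.6%. Other assumed correlations, with the PHQ-9 confined to its entry range, gave about 0.2% to 5%.

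**6. Simulation.** This used 55 per arm, weeks 0, 3 and 6, the PHQ-9 truncated to 10-16, and assumed correlations. For the group main effect, adding the PHQ-9 cut the variance by about 14%. For group-by-time it cut 0% with a main effect only and about 0.6% with PHQ-9-by-time.

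**7. Chance imbalance.** If scores are spread evenly over 10-16, the SD is 2.0. With 73 per arm (220/3), the 95% range of an arm difference is 1.96 × √(2/73) = ±0.32 SD, or about ±0.65 points. If one arm differs from the other two, f = 0.2 implies d = 0.2/√(2/9) = 0.42.
- Level contrast: shift up to 0.32 × 0.20 to 0.32 × 0.37 = 0.06-0.12 SD, roughly 15-28% of d.
- Change contrast: 0.32 × 0.03 to 0.32 × 0.05 = 0.010-0.016 SD, about 2-4% of d.

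**8. In terms of power.** On the basis of step 1, with f divided by √(1 − R²) and one degree of freedom fewer, where R² is the additional variance explained, power goes from 0.804 to 0.808 at R² = 0.01, 0.825 at 0.05 and 0.846 at 0.10.

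**The case against.** The strongest reply is that the model sentence is condensed. It names a random slope over time but no fixed time effect, although the stated aim is to examine improvement over four assessments. Read as a complete list it would describe an odd model, so a group-by-time term may well be intended, and covariates may be set in an analysis plan that is not shown. This stands in part: the absence of a covariate list is not in itself a fault. What remains is that the one model the article writes out does not use the score.

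A reader might infer that chance differences in severity go uncorrected. The documents do not support that. Baseline CESD-R is among the modelled assessments, and a group-by-time contrast removes most of such a difference: in the simulation, the estimate's dependence on PHQ-9 imbalance was −0.045 per point, against 0.143 for a group main effect. Nor is chance imbalance under valid randomisation a bias; the standard error and error rate already allow for it.

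A reader might also take 7-20%, or 16-57 participants, as the general size of the loss. Those figures hold only for the literal main effect, which averages in a baseline visit where no treatment effect can exist. The more direct cure for that is to specify the contrast.

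Finally, Participant timeline calls time 1 a preintervention assessment, so collection of baseline CESD-R after allocation is suggested and not established.

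**Conclusion.** The point holds as a minor, free improvement. The screening PHQ-9 is available for everyone before unrestricted allocation and is absent from the stated primary model. The gain from using it is about 7-20% of variance only if the treatment effect is a group main effect over visits. It is about 0-5%, or roughly 0-2 points of power, if the effect is group-by-time or baseline CESD-R is adjusted for. Every gain rests on assumed correlations and on a PHQ-9 confined to seven values.

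Two considerations make the change worthwhile despite the small expected gain. The article does not state which contrast will be tested, and the PHQ-9 remains usable if baseline CESD-R is incomplete or was collected after allocation.

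**What to change.** In Statistical methods:

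1. State the primary app-versus-placebo contrast after baseline, as a group-by-time effect on CESD-R.
2. Add the continuous screening PHQ-9 score and its interaction with visit as prespecified fixed effects in the primary CESD-R model. The interaction is needed, because a main effect alone gains nothing for a change contrast.
3. Report the same model without the PHQ-9 as a sensitivity analysis.

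Extending the adjustment to the secondary-outcome models is optional; nothing in the article shows a gain there. Stratified randomisation is not needed to obtain the precision. The cost is a sentence or two of text and a few model degrees of freedom, with no new data.
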